### Data analysis

All data will be analyzed using SAS (version 9.1, Cary, NC). For descriptive statistics, we will report mean and standard deviation or median and inter-quartile range for continuous variables and proportions for dichotomous variables. We will use the student t-test or Mann Whitney U test, where appropriate, for comparisons of continuous variables and the Chi square or Fisher exact test for comparisons of proportions.

The odds ratio for receiving a particular best practice, identified using process of care indicators performed in eligible patients, will be calculated in both groups using generalized linear mixed methods (glmm) to account for the hierarchical nature (clustering within centres) of the data[26]. The primary dichotomous outcome, the rate of change in proportion of patients receiving each best practice, will be analyzed by testing for the effects of group (targeted intervention versus control), time (during four months of intervention), and the interaction between group and time (the ratio of the odds ratio of improving over time in the targeted group versus the odds ratio in the control group). For secondary analyses, a before-after comparison will be performed in all hospitals to calculate the odds ratio for receiving each best practice following the active intervention phase. For hospitals that have already been assigned to receive a particular best practice prior to the crossover period, we will be able to monitor for declining use of the best practice following the crossover point (reported as ratio of odds ratios for receiving each best practice, after versus before).

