### Outcomes

The primary endpoint will be the difference in the rate of change in proportion of patients receiving each best practice in the actively targeted ICUs compared to the same practice in control ICUs during each four-month study phase. This will be described as the ratio of odds ratios for improvement over time for eligible patients receiving each best practice in the actively targeted ICUs compared to the same practice in control ICUs (odds ratio (actively targeted)/odds ratio (control)) and adjusted for clustering within centres. The unit of analysis for this endpoint will be the individual patient.

Secondary endpoints will include the rate of improvement over time in actively targeted ICUs and the rate of improvement over time in control ICUs; the proportion of eligible patients receiving each best practice during the final month of the study phase in active ICUs versus control ICUs; and the proportion of eligible patients receiving each best practice in actively targeted ICUs one year after the initial intervention. We will collect information on ICU length of stay and ICU mortality for descriptive purposes only. Limited clinical outcome measures will be measured for some best practices (for example, rate of catheter-related bloodstream infection). Health care worker satisfaction will be periodically measured using qualitative methodology.

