### Sample size

This study evaluates a planned quality improvement initiative involving a fixed number of ICUs over a defined funding period, so we performed a power rather than sample size calculation. Based on the results of our survey of ICU directors, we estimate that during a one-year period an average of 824 patients (range 307 to 1,700) will be admitted to each ICU. Since our study will involve 15 hospitals over two years, we expect that approximately 12,000 patients will be enrolled per study arm, and a total of 2,000 patients per four-month intervention phase. Assuming an average cluster size per phase of 250 patients and an intracluster (between centre) correlation coefficient (ρ) of 0.2 (variance inflation factor = 1 + (n-1)* ρ = 50; power = 80%; α = 0.05) [27], we should be able to detect a 20% increase when baseline adherence is 25%, a 30% increase when baseline adherence is 50%, or a 22% increase when baseline adherence is 75%.

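### The protocol names chi-square, Fisher, t and Mann-Whitney tests for comparisons without allowing for ICU clustering, and leaves the secondary final-month active-versus-control comparison open to them

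*Protocol article*

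**What the plan says.** The first paragraph of Data analysis opens with summary measures: "For descriptive statistics, we will report mean and standard deviation or median and inter-quartile range for continuous variables". The next sentence assigns hypothesis tests: Student's t or Mann-Whitney "for comparisons of continuous variables and the Chi square or Fisher exact test for comparisons of proportions". It mentions neither clustering nor any endpoint, and it does not restrict these tests to baseline or descriptive data.

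The second paragraph turns to the odds ratio for receiving a best practice, to be estimated "using generalized linear mixed methods (glmm) to account for the hierarchical nature (clustering within centres) of the data". It then specifies tests of group, time and their interaction for the primary outcome. The secondary analyses it lists are the before-after comparison and the check for declining use after the crossover.

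In Outcomes, the primary endpoint is to be "adjusted for clustering within centres". That phrase is not repeated for the secondary endpoints, one of which is "the proportion of eligible patients receiving each best practice during the final month of the study phase in active ICUs versus control ICUs". The same section announces limited clinical outcome measures for some practices, such as the catheter-related bloodstream infection rate, and says that ICU length of stay and ICU mortality are collected only for description.

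The Sample size section assumes an intracluster correlation of 0.2 and a variance inflation factor of 50.

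**The concern.** A chi-square or Fisher test on pooled patients takes its standard error from the number of patients. In this trial the randomised units are 15 ICUs in two groups, and the power calculation itself treats patients within an ICU as strongly correlated. A test that ignores this understates the variance of the between-arm difference and rejects a true null hypothesis far too often.

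The final-month endpoint is a between-arm comparison of proportions. The only sentence in Data analysis that attaches a test to comparisons of proportions in general is the chi-square/Fisher sentence, and the mixed-model paragraph does not mention the final month. An analyst following the text literally could therefore apply the unadjusted test to a named endpoint for each of six practices. The clinical outcome measures have no cluster-adjusted method named either, so any between-arm test of them is open to the same error.

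**Working it through.** **Inputs from the documents**
- Cluster size (Sample size): "Assuming an average cluster size per phase of 250 patients".
- Intracluster correlation 0.2, variance inflation factor (VIF) 50, α 0.05 (Sample size). Sidedness is not stated; two-sided is assumed.
- 15 ICUs in two groups (Randomization section); 8 versus 7 is assumed.
- Estimated eligible share by practice: 48% (lowest) to 76% (highest) (Selection of clinical best practices).

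**Step 1: the plan's own figure.** VIF = 1 + (m − 1) × ρ = 1 + 249 × 0.2 = 50.8, against the stated 50. It reproduces, apart from rounding.

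**Step 2: cluster size for a final month.** The protocol does not state this, so it is derived. All patients in one month of a four-month phase: 250 / 4 = 62.5 per ICU. At 76% eligible: 62.5 × 0.76 = 47.5. At 48% eligible: 62.5 × 0.48 = 30. The upper value of 62.5 would need every patient to be eligible, which is above the highest share in the survey.

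**Step 3: true type I error of an unadjusted two-sided 5% test.** The unadjusted z statistic has variance VIF instead of 1 under the null, so the error is 2 × [1 − Φ(1.96 / √VIF)].

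| Eligible patients per ICU in the month | ρ | VIF | True type I error |
|---|---|---|---|
| 30 | 0.2 | 1 + 29 × 0.2 = 6.8 | 45% |
| 47.5 | 0.2 | 1 + 46.5 × 0.2 = 10.3 | 54% |
| 62.5 | 0.2 | 1 + 61.5 × 0.2 = 13.3 | 59% |
| 30 | 0.05 | 1 + 29 × 0.05 = 2.45 | 21% |
| 62.5 | 0.05 | 1 + 61.5 × 0.05 = 4.08 | 33% |
| 30 | 0.01 | 1 + 29 × 0.01 = 1.29 | 8% |
| 62.5 | 0.01 | 1 + 61.5 × 0.01 = 1.62 | 12% |

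**Step 4: sensitivity to the monthly count.** Using the surveyed mean of 824 admissions a year instead gives 824 / 12 = 68.7 per month, and 33 at 48% eligible. With ρ = 0.2 the error is then 61% and 47%, so the range barely moves.

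**Step 5: simulation check.** Beta-binomial data for 8 versus 7 ICUs with ρ = 0.2, 20,000 runs per setting and a pooled chi-square test gave 45% to 46% at 30 patients per ICU and 59% at 62, for true proportions of 0.25, 0.50 and 0.75. The formula is adequate with this few clusters.

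**The case against.** The best defence is that the sentence on simple tests sits directly after the one on descriptive statistics, before any group or endpoint is mentioned, and may have been meant only for descriptive comparisons. The second paragraph of Data analysis also opens broadly: the odds ratio for receiving a best practice, in both groups, comes from a mixed model, and a group effect is tested as well as the interaction. Final-month adherence could fall under that. Moreover, this is a condensed article, and the method for each secondary endpoint is often left to a separate analysis plan.

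That reading is plausible, but the text does not state it. The simple-test sentence speaks of comparisons, names hypothesis tests and carries no limit. The point concerns a method that is stated and does not fit the design, not a detail left for later.

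Much of the objection does stand, and it rules out several stronger readings that a reader might infer:
- *That the primary result is at risk.* It is not; its model accounts for clustering.
- *That the error reaches about 78%.* That value needs a whole-phase unadjusted comparison with 250 patients per ICU (VIF 50.8). No listed endpoint is shown to be one.
- *That the same rates apply to continuous outcomes or to clinical outcome measures.* The value of 0.2 appears only in the power calculation for adherence, and no correlation is given for anything else. Length of stay and ICU mortality are for description only.

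**Conclusion.** The concern holds in a limited form. As written, the protocol permits tests that ignore the unit of randomisation, and it does not expressly give final-month adherence to the clustered model. If chi-square or Fisher were applied to that endpoint, the true type I error of a nominal 5% test would be about 45% to 59% at the plan's correlation of 0.2, and about 21% to 33% at 0.05. These figures assume two-sided testing, about 30 to 62 eligible patients per ICU in the final month (250 / 4 with 48% to 100% eligible), roughly equal cluster sizes, and a single month having the same correlation as that assumed for the phase. They describe what would happen under one permitted reading; the documents do not establish that the sponsor intends it. For the clinical outcome measures the direction of the error is the same wherever ICUs differ, but its size cannot be given.

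**What to change.** Amend Data analysis in two places.

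1. State that the t, Mann-Whitney, chi-square and Fisher tests are not used for between-arm inference.
2. State that every between-arm outcome comparison, including final-month adherence and any tested clinical outcome measure, uses one of two methods: the mixed model with an ICU random effect, taking the active-versus-control contrast at the final month; or an analysis of ICU-level summaries, with 15 − 2 = 13 degrees of freedom.

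This changes wording only; design and data collection stay as they are. The cost is wider standard errors. Relative to the unadjusted test at a correlation of 0.2, they grow by a factor of about √6.8 = 2.6 to √13.3 = 3.6 for the final-month comparison, which is the uncertainty that the plan's own assumption implies.

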### Randomization of participating ICUs and best practices

The 15 community ICUs will be randomly allocated into two groups (central computer-generated randomization with allocation concealment), with stratification by ICU size (≤ 10 versus > 10 staffed beds). The six best practices will be divided into the following three pairs to ensure that each does not impact on the same primary patient endpoint: 1) anticoagulation for prophylaxis against venous thromboembolism with semi-recumbent positioning to prevent ventilator-associated pneumonia; 2) sterile precautions for central venous catheter insertion to prevent catheter-associated bacteremia, with daily spontaneous breathing trials to decrease duration of mechanical ventilation; 3) early enteral nutrition with daily assessment of risk for developing decubitus (pressure) ulcers. These three pairs will be implemented in six phases according to a computer-generated random schedule, each four months long during the first year and, following the crossover point (Figure 2), three months long during the second year. The participating ICUs will be given their group assignments by the project coordinator at the start of each study phase. Although blinding within ICUs is not possible, they will be blinded to the other study arm's intervention.

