The study design incorporates several unique features that merit attention. First, the cluster-randomized approach will enable inter- and intra-ICU comparisons of performance, and enable adjustment for unit-level factors that might affect utilization of best practices. Second, the active control arm ensures that all ICUs are engaged in quality improvement activities during each study phase (each ICU simultaneously functions as an intervention unit and a control unit), and avoids the perceptions of unfairness that would arise from randomizing individual ICUs to no quality improvement. Finally, the design allows for longitudinal before-after comparisons for units that are originally assigned to receive the control phase for a given best practice, and for assessment of decay in the use of a best practice for ICUs initially assigned to the intervention phase. We believe this unique study design should be appealing to policy makers and funding bodies interested in studying future system-level initiatives in the ICU and in other areas of healthcare.

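### The primary test is a difference in time trends between randomised ICUs, but the described mixed model does not say that ICU trends may vary; if they do, a centre-intercept model rejects too often

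*Protocol article*

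**What the plan says.** The Outcomes section defines the primary endpoint as "the difference in the rate of change in proportion of patients receiving each best practice in the actively targeted ICUs" compared with the control ICUs. It is reported as a ratio of odds ratios and "adjusted for clustering within centres". The section adds: "The unit of analysis for this endpoint will be the individual patient".

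The Data analysis section fits the model "using generalized linear mixed methods (glmm) to account for the hierarchical nature (clustering within centres) of the data". It then says that the primary outcome "will be analyzed by testing for the effects of group (targeted intervention versus control), time (during four months of intervention), and the interaction" of the two. That lists the tested effects. The section does not say which random effects the model carries, or which reference distribution the interaction test uses.

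Under the randomisation heading, the 15 community ICUs are split into two groups "with stratification by ICU size (≤ 10 versus > 10 staffed beds"). The Data analysis section does not mention this stratum. The Discussion says that the design will "enable adjustment for unit-level factors that might affect utilization of best practices", without giving a model.

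**The concern.** The ICUs are what is randomised, so the group-by-time effect is a contrast between the trends of one set of ICUs and those of another, 15 trends in all. A random intercept for centre removes differences in starting level. It does nothing about ICUs that improve or decline at different speeds. If such variation exists and is not in the model, the interaction is judged against patient-level sampling error alone, and chance differences in drift between the two groups can pass for an effect of the campaign.

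Some variation in trend is plausible. The Participating ICUs section reports seven closed, one mixed and seven open units, with 4 to 19 staffed beds and ventilation in 10 to 65% of patients. These are baseline features and do not measure drift, but they make identical trends in all 15 units a strong assumption. The same model serves all six practices, so the primary result of each is exposed.

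**Working it through.** **Inputs from the protocol.** There are 15 ICUs (taken as 7 versus 8), an average cluster size of 250 per phase, an ICC of 0.2, four months of follow-up and α = 0.05. The plan's only cluster parameter is this ICC. It gives 1 + 249 × 0.2 = 50.8, stated as 50, and it describes variation in level. The protocol states no variance for trends, so there is no figure of its own to reproduce for the interaction test.

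**Patients per ICU-month.** All admissions: 250 / 4 = 62.5. Eligibility by practice is put at 48 to 76%, so eligible patients number about 0.48 × 62.5 = 30 to 0.76 × 62.5 = 47.5.

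**Assumed input.** The between-ICU SD of the monthly log-odds slope, s, is not in the protocol. On the latent logit scale, an ICC of 0.2 implies a between-ICU SD in level of √(0.2/0.8 × π²/3) = √0.8225 = 0.91. Over three monthly steps:
- s = 0.05 gives a one-SD drift of 0.15 log-odds (50% to 53.7%)
- s = 0.1 gives 0.3 (50% to 57.4%)
- s = 0.2 gives 0.6 (50% to 64.6%)
- s = 0.3 gives 0.9, as large as the whole baseline spread. It is treated as extreme and left out of the conclusion.

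**Analytic approximation.** With m patients per ICU at four equally spaced months (variance of time = 1.25) and a baseline of 50%, the average of p(1−p) over ICUs is about 0.212. The sampling variance of one ICU's slope is then v = 1/(m × 0.212 × 1.25), and the true variance is v + s². A test that assumes v alone is off by r = 1 + s²/v, and its type I error is 2[1 − Φ(1.96/√r)].

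- m = 250: v = 0.0151. For s = 0.2, r = 1 + 0.04/0.0151, about 3.66 (before rounding v), and 1.96/√3.66 = 1.02, which gives 30.5%.
- m = 125 (31 per month): v = 0.0301. For s = 0.2, r = 2.33, which gives 19.9%.

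**Simulation with no true interaction.** Simulation A fitted centre intercepts as fixed effects (1,500 trials per cell). Simulation B fitted a random-intercept logistic model by adaptive quadrature (700 trials per cell).

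| s per month | Analytic, m = 125 | Analytic, m = 250 | A, 40 per month | A, 62 per month | B, m = 250 |
|---|---|---|---|---|---|
| 0 | 5.0% | 5.0% | 4.7% | 5.5% | 4.7% |
| 0.05 | 6.0% | 7.0% | – | – | 6.6% |
| 0.1 | 8.9% | 12.9% | 10.4% | 13.7% | 11.0% |
| 0.2 | 19.9% | 30.5% | 22.3% | 30.5% | 32.7% |

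Simulation B with m = 125 and s = 0.2 gave 18.6%, with a Monte Carlo standard error of √(0.186 × 0.814/700) = 1.5 points, in line with the analytic 19.9%. A further simulation over 30 to 62 eligible patients per ICU-month gave about 8–13% at s = 0.1 and 20–30% at s = 0.2.

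**Comparator.** A t-test on ICU-specific slopes (13 degrees of freedom) rejected in 3.9–5.8% of trials in simulation A and 4.0–7.3% in B, whatever the slope SD.

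**Reference distribution.** Once the comparison rests on ICU slopes, a cut-off of 1.96 on 13 degrees of freedom has a two-sided size of 7.2%, so the degrees of freedom matter too.

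**Bed-size stratum.** In simulation B, leaving the stratum out gave a type I error of 4.4% when strata differed in level by 1.0 logit (4.1% with the stratum in the model), and 5.3% when strata differed in slope by 0.2 per month. There was no inflation. In that last setting the unadjusted slope t-test rejected in only 1.3% of trials. It was conservative because stratum differences in slope sat in its error term, and that is the precision a stratum-by-time term can recover.

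**The case against.** The strongest reply is that the charge is read from silence. The Data analysis section lists the effects to be tested, which is the fixed part. A mixed model for centre clustering can carry random slopes as well as intercepts, and a condensed article often leaves that to a fuller document. This stands in part: a reader might infer that the protocol commits to an intercept-only model, and it does not say so. But the article does fix the slope endpoint, the tested terms, the patient as unit and a single adjustment for centre. Together these most naturally describe the centre-intercept model.

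Three further inferences are tempting and are not supported:
- **That 15 ICUs alone make the test anti-conservative.** At zero slope variance the rejection rate was about 5%. The inflation comes from varying trends.
- **That omitting the bed-size stratum inflates type I error.** The simulations show that it does not. A centre intercept already absorbs level differences, so a bed-size main effect adds little to the interaction estimate.
- **That the plan analyses patients as though they had been individually randomised.** It adjusts for centre and applies a variance inflation factor of 50 in its power calculation. What is not visible is an allowance for clustering of trends.

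It is also fair that the slope SD is assumed, and that figures based on all 250 admissions overstate the case for practices with fewer eligible patients. The ranges given cover the smaller counts.

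**Conclusion.** The concern holds conditionally. The protocol leaves open whether ICU trends may vary in the primary model, and on the natural reading they may not. Under that reading, a nominal 5% test of group-by-time has a type I error of about 5% if all ICUs share one trend in the absence of an effect, 5–7% at a slope SD of 0.05 log-odds per month, 8–14% at 0.1 and 20–33% at 0.2. This assumes roughly 30 to 62 eligible patients per ICU-month, an ICC of 0.2 on the latent logit scale and a 1.96 cut-off. The random-intercept simulation and the analytic approximation also assume 50% baseline adherence. A test on ICU-specific slopes holds at about 4–7%.

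This is an under-specified primary test with a plausible and possibly large consequence, not a demonstrated error. It should be fixed.

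**What to change.** State the random part of the primary model: a random intercept and a random time slope for ICU, or a random ICU-by-month effect in addition to the intercept. Test group-by-time with between-cluster degrees of freedom (15 − 2 = 13, fewer with added cluster-level terms), or by a permutation test over the allocations that the stratified randomisation could have produced.

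As a secondary change, to reflect the design and for precision only, include the bed-size stratum and its interaction with time as fixed effects.

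No new data are needed. Intervals widen to reflect variation between ICUs, and the stratum terms use one or two of the roughly 13 degrees of freedom.

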### Sample size

This study evaluates a planned quality improvement initiative involving a fixed number of ICUs over a defined funding period, so we performed a power rather than sample size calculation. Based on the results of our survey of ICU directors, we estimate that during a one-year period an average of 824 patients (range 307 to 1,700) will be admitted to each ICU. Since our study will involve 15 hospitals over two years, we expect that approximately 12,000 patients will be enrolled per study arm, and a total of 2,000 patients per four-month intervention phase. Assuming an average cluster size per phase of 250 patients and an intracluster (between centre) correlation coefficient (ρ) of 0.2 (variance inflation factor = 1 + (n-1)* ρ = 50; power = 80%; α = 0.05) [27], we should be able to detect a 20% increase when baseline adherence is 25%, a 30% increase when baseline adherence is 50%, or a 22% increase when baseline adherence is 75%.

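### The stated 80% power for a 20% increase from 25% baseline adherence does not follow from the plan's own inputs, which give about 47%, and the calculation is not for the primary group-by-time test

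*Protocol article*

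**What the plan says.** All of the following is in the protocol article.

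- **Sample size, inputs.** The plan expects "approximately 12,000 patients will be enrolled per study arm, and a total of 2,000 patients per four-month intervention phase". It assumes "an average cluster size per phase of 250 patients" and an "intracluster (between centre) correlation coefficient (ρ) of 0.2", giving "variance inflation factor = 1 + (n-1)* ρ = 50", with "power = 80%; α = 0.05". Whether α is one- or two-sided is not stated.
- **Sample size, result.** From this one set of inputs it concludes that "we should be able to detect a 20% increase when baseline adherence is 25%, a 30% increase when baseline adherence is 50" per cent, and adds a 22% increase from a baseline of 75%. It does not say whether the increases are absolute or relative.
- **Randomization of participating ICUs and best practices.** "The 15 community ICUs will be randomly allocated into two groups". Under Participating ICUs, the academic ICU is kept out of the primary analyses.
- **Outcomes and Data analysis.** "The primary endpoint will be the difference in the rate of change in proportion of patients receiving each best practice", active versus control, expressed as a ratio of odds ratios. It is tested through the interaction of group and time in a generalized linear mixed model.

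**The concern.** By the symmetry of the binomial variance around 50%, a rise from 25% into the middle of the scale should be about as hard to detect as a rise from 50% to 80%. The plan nevertheless gives 20 for the first and 30 for the second. A rise from 75% runs into the low-variance end of the scale, so its smaller figure of 22 makes sense; the 20 has no such explanation.

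The calculation also uses only a baseline proportion, an increase and a variance inflation factor. It has no time slope and no within-ICU correlation over time, so it looks like power for a difference in levels, not for the endpoint declared primary.

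At stake is how a null result is read. Someone relying on this paragraph would take a null finding for a practice with low baseline use as evidence against a 20-point effect. The paragraph does not support that.

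**Working it through.** **Inputs** (Sample size section): 250 patients per ICU per phase; ρ = 0.2; variance inflation factor 50 as printed (exactly 1 + 249 × 0.2 = 50.8); α = 0.05, taken as two-sided; power 80%.

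**Patients per arm.** 12,000 per arm / 6 phases = 2,000 per arm per phase. From the admission estimate, 824 × 15 / 3 = 4,120 for both arms in a four-month phase, or 2,060 per arm. So 2,000 is a per-arm number, although it is called a total.

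**Effective sample size.** 2,000 / 50 = 40 per arm (39.4 with 50.8).

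**Formulas.** With Δ = p2 − p1, p̄ = (p1 + p2)/2, SE1 = √{[p1(1−p1) + p2(1−p2)]/40} and SE0 = √{2p̄(1−p̄)/40}:

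- unpooled power = Φ(Δ/SE1 − 1.96)
- pooled power = Φ[(Δ − 1.96·SE0)/SE1]

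**The two figures that reproduce.**

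- 50% to 80%: SE1 = √(0.41/40) = 0.1012 and SE0 = 0.1067. Unpooled Φ(2.96 − 1.96) = 0.84; pooled Φ[(0.30 − 0.209)/0.1012] = 0.82.
- 75% to 97%: SE1 = √(0.2166/40) = 0.0736 and SE0 = 0.0776. Unpooled Φ(2.99 − 1.96) = 0.85; pooled Φ[(0.22 − 0.152)/0.0736] = 0.82.

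**The figure that does not.**

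- 25% to 45%: SE1 = √(0.435/40) = 0.1043 and SE0 = 0.1067. Unpooled Φ(1.92 − 1.96) = 0.483; pooled Φ[(0.20 − 0.209)/0.1043] = 0.465.

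| Baseline | Printed increase | Power, pooled / unpooled | Rise detectable with 80% power (pooled) |
|---|---|---|---|
| 25% | 20 | 0.465 / 0.483 | 30.3 points |
| 50% | 30 | 0.82 / 0.84 | 29.5 points |
| 75% | 22 | 0.82 / 0.85 | 21.6 points |

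With the exact factor of 50.8, power at 25% is 0.459 / 0.477 and the detectable rise is about 30.6 points.

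**What a 20-point rise from 25% would need.** n = [1.96√(2 × 0.35 × 0.65) + 0.84√0.435]² / 0.20² ≈ 89 effective patients per arm. That is 89 × 50 = 4,450 actual patients per arm, or about 18 ICUs per arm at 250 each.

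**Other readings of the sentence** (power for the 25%, 50% and 75% baselines in turn):

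- One-sided α = 0.05: 0.59–0.61 at 25%; the other two rise to about 0.89–0.91.
- Relative increases (25% to 30%, 50% to 65%, 75% to 91.5%): 0.07, 0.27–0.28, 0.51–0.53.
- 2,000 as the total for both arms: 0.26–0.27, 0.51–0.55, 0.52–0.56.

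None gives 80% at 25%. Only the absolute, two-sided, per-arm reading reproduces the other two figures.

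**Fifteen ICUs.** An even split is impossible, so 7 versus 8 is the closest; this is inferred, not printed. At 250 per ICU the arms have 1,750 and 2,000 patients, and the same normal formula gives 0.43–0.46 for 25% to 45%. Replacing the normal reference by a cluster-level t-test on 13 degrees of freedom lowers this to about 0.40.

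**Which comparison this is.** The 250 per ICU covers a whole four-month phase, and the formula compares adherence between arms over that phase. It is neither the primary group-by-time interaction nor the secondary final-month comparison, which would have about 250 / 4 ≈ 62 patients per ICU.

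**The case against.** The strongest reply is that little depends on the figure. The plan says that the number of ICUs and the funding period are fixed and that it computed power, not a sample size. Correcting the paragraph changes no recruitment, design or analysis. No practice is stated to have 25% baseline adherence, so the affected scenario is hypothetical. These points stand and limit the seriousness, but they do not make the figure right.

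The allocation matters less than it may seem. A reader might infer from 2,000 / 250 = 8 that a sixteenth ICU was counted. But 2,000 also follows from 12,000 / 6, and 7.5 ICUs × 275 (824 / 3) is 2,060, so a rounded cluster size explains it equally well. The 7 versus 8 split alone costs 2 to 3 percentage points of power. The 40% needs the t reference as well, which the Data analysis section does not specify.

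A tempting stronger reading is that the trial has even odds or worse of detecting a 20-point effect. The document does not support that. The 47% belongs to a comparison of levels. A test of change within ICUs removes stable differences between ICUs and could do much better, or worse if trends vary widely between ICUs. The document gives neither the between-ICU variance in trend nor the month-to-month correlation, so any figure would rest on the reader's assumptions.

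**Conclusion.** Wrong as written; a should-fix correction of the stated power. Under the plan's own inputs, power for 25% to 45% is about 47%, not 80%, and the detectable rise from 25% is about 30 percentage points, not 20. This rests on a two-sided α of 0.05, 2,000 patients per arm and absolute increases, the reading under which the other two printed figures come out. With 7 versus 8 ICUs the power is about 43% to 46%, or about 40% with a 13-df t-test as well.

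Separately, none of the three figures is power for the primary group-by-time test. Whether that test is well or badly powered is unknown from this document.

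**What to change.** In the Sample size section:

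1. Replace the 20% increase at 25% baseline with about 30 percentage points.
2. Write percentage points for all three increases, and state that α is two-sided.
3. Label the 2,000 patients per phase as per arm.
4. State that the figures are for a between-arm comparison of whole-phase adherence levels and not for the primary group-by-time test. They should not be labelled as end-of-phase figures, because the end-of-phase endpoint uses the final month only.
5. Add power for the group-by-time interaction over a stated range of assumptions about between-ICU variation in trend.

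The first four items reword one paragraph; the fifth needs a short calculation or simulation. One figure becomes less favourable. No extra patients or ICUs are needed.
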